### 8.2. Statistical Analysis

#### 8.2.1. Baseline Characteristics

To compare baseline measures between groups, inferential analyses will be conducted using Student’s *t*-test for independent samples when the assumptions of normality and homogeneity of variance are met, or the Mann–Whitney U test when these assumptions are not satisfied.

#### 8.2.2. Analysis of the Outcome Measures

In alignment with the CONSORT (Consolidated Standards of Reporting Trials) guidelines for randomized controlled trials, a per-protocol analysis will be undertaken. The Shapiro–Wilk test, along with visual inspection of boxplots and histograms, will be employed to evaluate the assumption of normality, while Levene’s test will be used to assess the homogeneity of variances. Descriptive statistics, including mean ± SD, frequencies, and percentages, will be used to summarize the baseline characteristics of the participants. To investigate the acute and follow-up effects of E_tDCS_ and E_SHAM_, a 2 × 5 repeated measures ANOVA (two groups × five time points: baseline, post-intervention, 1-month, 3-month, and 6-month follow-ups) will be conducted. Main effects (time and group) and interaction effects (group × time) will be analyzed using SPSS version 28 (IBM Corp., Armonk, NY, USA) and JASP (Version 0.15.0.0.0; JASP Team, Amsterdam, The Netherlands, 2023). In instances where significant interactions are identified, pairwise post hoc comparisons with Bonferroni correction will be conducted. Cohen’s d and 95% confidence intervals (CIs) will be used to report effect sizes and the magnitude of observed changes. If the data violate parametric assumptions, non-parametric alternatives (for example, Mann–Whitney test) will be applied. In the event of participant attrition or a decrease in statistical power below the predefined 80% threshold, an intention-to-treat analysis will be conducted to ensure the robustness of the findings [67]. All statistical analyses will be performed using JASP software (version 0.18.3.0; JASP Team, Amsterdam, The Netherlands) by an independent statistician who is blinded to group allocation and uninvolved in data collection.

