## 4. Sample Size

The sample size will be determined using G*Power software (Franz Faul, University of Kiel, Kiel, Germany; version 3.1.9.2). Statistical analysis will be conducted using repeated measures analysis of variance (ANOVA). The calculation will be based on the primary outcome variable, the Oswestry Disability Index (ODI), with the assumption of a Cohen’s effect size of 0.81 [26], a statistical power of 0.95, an alpha error of 0.05, and two study groups. The estimated total sample size is 30. To accommodate a potential dropout rate of 40% during follow-up, the minimum required number of participants has been adjusted to 42 (experimental group = 21; control group = 21). This rate is consistent with previous evidence: a review of clinical studies on chronic pain reported that dropout can vary widely, ranging from 5% to 60% depending on the study, type of pain, duration, and intervention. The selected effect size is categorized within a large range (0.60–1.19), as corroborated by previous studies [27].

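### The named analysis of the ODI is per-protocol; intention-to-treat enters only on an attrition or power trigger and is not ranked against it

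*Protocol article*

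**What the plan says.** Section 8.2.2 (Analysis of the Outcome Measures) opens with the analysis set: "In alignment with the CONSORT (Consolidated Standards of Reporting Trials) guidelines for randomized controlled trials, a per-protocol analysis will be undertaken". It then describes a repeated measures ANOVA of two groups by five time points. Near the end comes the conditional rule: "In the event of participant attrition or a decrease in statistical power below the predefined 80% threshold, an intention-to-treat analysis will be conducted". The purpose given for this second analysis is the robustness of the findings.

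Section 4 (Sample Size) bases the calculation on the ODI with "a statistical power of 0.95, an alpha error of 0.05, and two study groups". It reports that "The estimated total sample size is 30" and continues: "To accommodate a potential dropout rate of 40% during follow-up, the minimum required number of participants has been adjusted to 42". It also cites a dropout range of 5% to 60% in chronic pain studies.

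Two other places bear on who is analysed. Section 8.1 (Data Collection) has incomplete returns taken out of the data. Section 6 measures adherence by completion of all the planned assessments. Neither is linked to the per-protocol set, which is not defined in the article.

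**The concern.** Randomisation makes the two arms comparable at allocation. A per-protocol set then removes patients for what they do afterwards, such as stopping sessions or missing visits. If the reasons for leaving differ between active and sham stimulation, the remaining patients are no longer comparable, and the difference in ODI can be biased in either direction.

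The conditional rule does not repair this. It makes the analysis set depend on attrition or on achieved power, both known only once data are in. It also gives no order of precedence. If the per-protocol and intention-to-treat results disagree, the plan does not say which one answers the primary question. In a trial of 42 that allows for 40% loss, the two sets could differ by many patients.

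**Working it through.** **1. The plan's own figure.** Inputs from section 4: 30 before dropout, 40% dropout. 30 × (1 + 0.40) = 42, which matches the stated total of 21 per arm. (Whether multiplying by 1.4 is the right inflation is a separate point.)

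**2. Size of a completers' set at the planned dropout.** 42 × (1 − 0.40) = 25.2, so about 25 patients, fewer than the 30 that section 4 requires. This assumes that the per-protocol set is roughly the completers. Sections 6 and 8.1 point that way, but the article does not say so.

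**3. How likely the attrition trigger is to fire.** As worded, one lost participant is enough. With independent losses at rate d, P(no loss among 42) = (1 − d)^42.

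| Dropout d | P(no loss) |
|---|---|
| 40% (planned) | 0.6^42 = 5 × 10⁻¹⁰ |
| 20% (illustrative) | 0.8^42 = 9 × 10⁻⁵ |
| 5% (low end of the cited range) | 0.95^42 = 0.12 |

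In practice both analyses will exist.

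**4. Which analysis then decides.** The rule says that intention-to-treat will be carried out and gives robustness as its purpose. It does not say that it replaces the per-protocol result, and no other section ranks the two. The power limb of the trigger adds no clarity. The 80% is called predefined, but the only power set elsewhere is 0.95, and how a fall in power would be judged is not stated.

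**5. Illustration of the bias.** The assumptions below are not in the document: no true effect; 40% lost in each arm; loss unrelated to outcome in one arm; in the other, the 60% retained are selected on a latent variable that has correlation r with the outcome; outcome SD of 1 in both retained groups.

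- Mean shift in the selected arm = r × φ(z₀.₄) / 0.6, with z₀.₄ = −0.253 and φ = 0.386, so 0.386 / 0.6 = 0.644 and the shift is 0.644r.
- r = 0.3: 0.19 SD. r = 0.5: 0.32 SD.
- Patients per arm: 21 × 0.6 = 12.6, so df = 23.2. Noncentrality = shift × √(12.6 / 2): 0.48 and 0.81.
- Two-sided rejection rate at a nominal 5%, from the noncentral t: 7.5% and 12%.

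A simulation that kept 13 of 21 per arm gave 7.3% and 12%. For scale, section 4 assumes an effect of 0.81, which is 0.81 SD if it is a standardised mean difference; the article says only that it is a Cohen's effect size.

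**6. When losses are random.** In a simulation of 20,000 trials with no true effect and purely random losses, the completers' test and the test of all 42 each held close to 5% (4.7% and 4.9%). The harm in step 5 therefore comes from outcome-related loss, which a plan that allows for 40% dropout cannot rule out.

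**The case against.** The strongest reply is that intention-to-treat will be run anyway. This is largely right. A reader might infer that the randomised comparison is lost altogether, and the document does not support that: at 40% dropout the trigger is all but certain to bring the comparison in. It is demoted or left unranked, which is the narrower defect described here.

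The two sentences can also be read together as per-protocol main and intention-to-treat supportive. On that reading the order is settled, but the wrong set is primary. On the other reading the order is open. Either way the wording needs changing.

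A reader might also infer that the 80% threshold contradicts the planned power of 0.95. It does not: a trial can be designed for 95% and still name 80% as a minimum. What stands is that the threshold is set nowhere else and that its use is not explained.

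It is equally tempting to say that the intention-to-treat run would still drop every patient with a missed visit, because a standard repeated measures ANOVA needs complete records. The article does not say how missing values enter that run. Imputation beforehand is compatible with the text, and such detail may be in a document not shown. The removal of incomplete returns in section 8.1 makes a completers' analysis more likely but does not establish it.

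Finally, section 8.2.2 gives the analysis to an independent statistician blinded to allocation. This limits deliberate choice by result, and the document gives no ground to suspect any. It does not undo selection after randomisation or decide which analysis counts.

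**Conclusion.** The rule is wrong as written. It is a stated choice, not a detail left for an analysis plan: the article names a per-protocol analysis for the outcome measures and makes intention-to-treat conditional on attrition or power, without saying which decides the ODI comparison.

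That the trigger will almost surely fire rests only on the plan's own dropout figures and independent losses. The bias of about 0.2 to 0.3 SD and the type I error of about 7.5% to 12% are illustrative. They need loss related to outcome in one arm only, at a moderate strength that the document neither gives nor excludes. They show what can happen and do not predict what will. Because the rule governs the primary conclusion, it should be corrected before any outcome data are analysed.

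**What to change.** In section 8.2.2, state that the primary ODI analysis includes all randomised participants in the arm to which they were allocated, whatever the attrition or achieved power. Name a method that keeps patients with missed visits, for example a likelihood-based mixed model using every available ODI value, or multiple imputation. Both rely on data being missing at random, so neither is guaranteed to remove the bias illustrated above if leaving depends on unobserved outcomes.

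Delete the attrition and 80% power trigger. Define the per-protocol set and keep that analysis as a supportive sensitivity analysis. Reconcile section 8.1, so that a participant with an incomplete return is not removed from the primary analysis.

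The cost is a change of wording and a little more analysis work. No new data, visits or patients are needed.

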## 3. Randomization and Blinding

Participants will be randomly allocated to either the intervention or control group through a stratified randomization process to ensure a balanced distribution based on neuropathic pain levels. Baseline neuropathic pain will be evaluated using the Douleur Neuropathique 4 (DN4) questionnaire, resulting in the formation of two strata: Subgroup 1, with DN4 scores of 4–7, and Subgroup 2, with DN4 scores of 8–10. An independent researcher will generate the randomization sequence, which will be securely stored on an encrypted USB device with restricted access, to be accessed solely for participant allocation. The study will employ a double-blind design, with participants blinded via a sham intervention and outcome assessors blinded to group allocation, without involvement in the intervention delivery. Additionally, follow-up data will be collected and recorded by the same independent researcher to ensure impartiality and data integrity. All intervention sessions will be conducted by experienced physiotherapists, each with over ten years of expertise in neuromodulation and exercise therapy for chronic lower back pain, ensuring consistent application of the treatment protocols.

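### The primary ODI analysis counts baseline as an outcome level and names no single effect, visit or contrast as the primary test

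*Protocol article*

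**What the plan says.** Section 4 sizes the trial on ODI and names the method: "Statistical analysis will be conducted using repeated measures analysis of variance (ANOVA". Section 8.2.2 gives the model as "a 2 × 5 repeated measures ANOVA (two groups × five time points: baseline, post-intervention, 1-month, 3-month, and 6-month follow-ups", so baseline ODI is part of the response. It continues: "Main effects (time and group) and interaction effects (group × time) will be analyzed using SPSS". Individual comparisons depend on the interaction: "In instances where significant interactions are identified, pairwise post hoc comparisons with Bonferroni correction will be conducted". Estimates are promised in general terms: "Cohen’s d and 95% confidence intervals (CIs) will be used to report effect sizes and the magnitude of observed changes". They are not tied to a visit or contrast.

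Section 3 allocates patients "through a stratified randomization process to ensure a balanced distribution based on neuropathic pain levels", with strata defined as "Subgroup 1, with DN4 scores of 4–7, and Subgroup 2, with DN4 scores of 8–10". The model in Section 8.2.2 has no DN4 term.

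The visit schedule differs between sections:
- Section 2.4 lists four collections: before treatment and at 1, 3 and 6 months.
- Section 8.2.2 lists five time points, including one labelled post-intervention.
- Table 1 shows five ODI collections, but the fifth is study completion. No visit there is labelled post-intervention.

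**The concern.** Randomisation rules out a treatment difference at baseline. A group main effect averaged over five levels therefore includes one level where the expected difference is zero. The group × time interaction does test whether the arms diverge, but it spends 4 degrees of freedom on the question. When significant, it does not say at which visit or in which direction the arms differ.

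The two tests answer different questions and neither is designated primary. A report could rest on either one, and the reader would have no pre-named ODI difference to look for. The trial plans on 30 analysable patients, so efficiency matters. Baseline ODI and DN4 stratum are both collected anyway, and both could be used as covariates.

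**Working it through.** **The plan's own figure.** Section 4 gives effect size 0.81, power 0.95, alpha 0.05, two groups, total 30, raised to 42 for 40% dropout. The 42 is 30 × 1.4. The 30 does not follow from these inputs alone, because the effect metric (d or f), the number of measurements and the correlation are not stated. Read as d = 0.81 in a two-sided two-sample t-test, 95% power needs 82 in total, and 30 gives 57%. This does not prove 30 wrong. It is used below as the planned analysable number, 15 per arm.

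**Assumptions not in the documents.** 0.81 is a between-arm difference in SD units; compound symmetry; between-visit correlation ρ from 0.3 to 0.8; two-sided alpha 0.05; five time points as in Section 8.2.2.

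**Formulas for a sustained effect** (0 at baseline, 0.81 at each of four later visits). The t-type noncentrality is (difference / SD) × √(15/2).

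- Group main effect: difference 0.81 × 4/5 = 0.648; variance (1 + 4ρ)/5. At ρ = 0.5: 0.648/√0.6 × 2.739 = 2.29. At ρ = 0.7: 0.648/√0.76 × 2.739 = 2.04.
- Interaction: λ = (30/4) × Σ(eₜ − ē)²/(1 − ρ), with Σ = 0.81² × 4/5 = 0.525; F on 4 and 112 df. At ρ = 0.5: 7.5 × 0.525/0.5 = 7.87. At ρ = 0.7: 13.1.
- Baseline-adjusted, one visit: difference 0.81; variance 1 − ρ². At ρ = 0.5: 0.81/√0.75 × 2.739 = 2.56. At ρ = 0.7: 3.11.
- Baseline-adjusted, mean of four follow-ups: difference 0.81; variance (1 + 3ρ)/4 − ρ². At ρ = 0.5: 0.81/√0.375 × 2.739 = 3.62. At ρ = 0.7: 4.16.

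Power at 15 per arm, sustained effect:

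| Test | ρ = 0.3 | 0.5 | 0.7 | 0.8 |
|---|---|---|---|---|
| Group main effect | 73% | 60% | 50% | 46% |
| Group × time | 43% | 58% | 82% | 95% |
| Adjusted, one visit | 60% | 68% | 84% | 94% |
| Adjusted, follow-up mean | 92% | 93% | 98% | >99% |

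The adjusted rows allow for estimating the baseline slope. The formulas above ignore that and come out about 1 point higher. Simulation agrees within its error.

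**Fading effect** (0.81 × 1, 0.75, 0.5, 0.25 over the four follow-ups), simulated, except that the interaction at ρ = 0.7 is the noncentral F value:

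| Test | ρ = 0.5 | 0.7 | 0.8 |
|---|---|---|---|
| Group main effect | 28% | 24% | 21% |
| Group × time | 47% | 71% | 89% |
| Adjusted, first post-baseline visit | 68% | 84% | 94% |
| Adjusted, follow-up mean | 57% | 69% | 82% |

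**Two candidate tests.** If a significant main effect or a significant interaction each counted as success, the chance of a false success would be 1 − 0.95² = 9.75% for independent tests. Simulation under the null gave 9.6%.

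**DN4 stratum** (assumed 2:1 split, ρ = 0.5, a time-constant stratum effect explaining 10 / 20 / 30% of variance; simulated). Without the stratum term, the main-effect test has type I error 3.5 / 2.1 / 1.2% and power 57 / 54 / 50%. With the term, power is 64 / 69 / 75%. In the baseline-adjusted analysis of the follow-up mean, the stratum term adds only about 1 point.

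**The case against.** The group × time interaction is a valid randomised comparison, so part of this point is a preference for efficiency. That is fair, and the advantage of adjustment is conditional. With a sustained effect, the interaction and the one-visit contrast are level at ρ = 0.7–0.8 (82% against 84%, then 95% against 94%). With a fading effect, the interaction matches or slightly beats the follow-up mean (71% against 69%, then 89% against 82%). A fading effect is plausible when visits continue after treatment ends. The one-visit contrast keeps its lead there only if the chosen visit is near the peak. The documents give no between-visit correlation. The test–retest range of 0.73–0.99 in Section 5.2 is a different quantity, but it lends no support to ρ = 0.5, where adjustment gains more than at 0.7 or 0.8.

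Four stronger readings are tempting, and the documents do not support them:
- A reader might infer that type I error is 9.75%. The text never says either test suffices, and only the interaction opens the pairwise comparisons. It leaves the matter open.
- A reader might infer that no treatment estimate will be given. Section 8.2.2 promises Cohen's d with 95% CIs. What is missing is one pre-named estimate.
- A reader might infer that omitting the DN4 stratum inflates false positives. For the main effect the error runs the other way, and the term matters little once baseline ODI is in the model.
- A reader might fault the silence on sphericity. The text does not say that the tests will be uncorrected, and such detail is commonly left to an analysis plan.

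What stands is that the article commits to a specific model with baseline in the response and designates no primary test within it.

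**Conclusion.** The point holds in this limited form. The dilution of the main effect from 0.81 to 0.65 SD is arithmetic and needs only a sustained effect and the five-level model. The absence of a designated effect, visit or contrast is plain from Section 8.2.2.

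The power comparison rests on assumed correlation, compound symmetry and effect profile. Adjustment clearly beats the group main effect at ρ of 0.5 or more in both profiles. Against the interaction it helps at ρ = 0.5 and may gain nothing at 0.7–0.8. For a sustained effect, the baseline-adjusted follow-up mean is the only option examined that comes near the stated 95% power with 30 patients across the whole correlation range. The analysis should be changed, since the improvement needs no new data, but the planned tests are not invalid.

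**What to change.** 1. Reconcile the visit schedule across Section 2.4, Table 1 and Section 8.2.2. Until then, a contrast at the end of the intervention cannot be tied to a scheduled visit.
2. Name one primary ODI contrast: the arm difference at one visit on the reconciled schedule, or the average over the post-baseline visits. Choose according to whether the effect is expected to last or fade. Treat other visits as supportive.
3. Estimate it in ODI points with its 95% CI, from a mixed model or ANCOVA on post-baseline ODI with baseline ODI and DN4 randomisation stratum as covariates. With this few patients, state a small-sample degrees-of-freedom method such as Kenward–Roger.
4. Include the stratum term to match the design, without expecting much power from it. Confirm which DN4 score defines the strata: Section 5.3.7 describes a 0–7 interview sub-score, on which the 8–10 stratum would be empty.

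The cost is analysis wording and about two model degrees of freedom. No extra patients, visits or measurements are needed.

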### 2.4. Procedure

Upon formation of the groups, four distinct sample collections will be undertaken at the following intervals: Pre, Post-1 month, Post-3 months, and Post-6 months (Figure 1). At each designated measurement point, a comprehensive follow-up of the studied variables will be meticulously conducted and recorded in the “Data Collection Notebook”. This document is specifically crafted to capture both primary and secondary variables, thereby ensuring a systematic approach to data collection throughout the study. The research comprises two groups, each structured to meet the previously outlined objectives: the E_tDCS_ and E_SHAM_ groups. All assessments will be performed bilaterally to enable within-subject comparisons.

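### Assumption checks on the trial data may replace the planned group × time analysis of ODI with a test that cannot address group × time, under an undefined trigger

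*Protocol article*

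**What the plan says.** All of this is in section 8.2.2 of the protocol article unless stated otherwise.

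- **Planned analysis:** a repeated measures ANOVA with "two groups × five time points: baseline, post-intervention, 1-month, 3-month, and 6-month follow-ups". On effects, the text says: "Main effects (time and group) and interaction effects (group × time) will be analyzed".
- **Normality check:** "The Shapiro–Wilk test, along with visual inspection of boxplots and histograms, will be employed to evaluate the assumption of normality".
- **Variance check:** "Levene’s test will be used to assess the homogeneity of variances".
- **Switch:** "If the data violate parametric assumptions, non-parametric alternatives (for example, Mann–Whitney test) will be applied".
- **Multiplicity:** Bonferroni-corrected pairwise comparisons are planned only where an interaction is significant.

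ODI is the primary outcome (section 5.2), and section 4 sizes the trial on it, "with the assumption of a Cohen’s effect size of 0.81", with 30 patients before the dropout allowance.

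The article does not give the significance level of the checks or their number. It does not say whether they apply to raw scores or residuals, how the plots and the tests are combined, or whether one failure is enough.

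**The concern.** The switch is a stated rule, so this is more than detail left to a fuller document. The rule lets the observed data choose the analysis of the primary outcome, and the replacement it names does not fit the planned question. The ANOVA asks whether the course of ODI over time differs between arms. A two-sample Mann–Whitney test asks whether one value per patient tends to be larger in one arm.

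Once the switch fires, three things are open: which visit is tested, whether raw scores or changes from baseline enter, and what correction applies across visits. The Bonferroni step does not settle the last point, because its condition is a significant interaction and the Mann–Whitney test produces none.

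At stake are a primary question that depends on the data, lost power in some settings, and room for several visit-level tests. The statistician's blinding limits deliberate choice but does not restore the question.

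**Working it through.** The plan gives no figure for how often the switch would occur, so there is none to reproduce.

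**Inputs from the article:** 2 arms and 5 time points (section 8.2.2); 30 patients, taken as 15 per arm (section 4); effect size 0.81 (section 4), read as Cohen's d.

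**Assumptions:** normal data, equal variances, the same correlation ρ between all visits, checks at the 5% level, and d = 0.81 at every follow-up with no difference at baseline.

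**1. How often the switch fires by chance**

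For k independent checks at 5%, the chance of at least one failure is 1 − 0.95^k.

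| What is checked | k | 1 − 0.95^k | Simulated, correlated visits |
|---|---|---|---|
| One visit: 2 Shapiro–Wilk + 1 Levene | 3 | 0.14 | 0.14–0.16 |
| One Shapiro–Wilk on model residuals + Levene at each visit | – | – | 0.17–0.28 |
| Shapiro–Wilk in all 10 arm-by-visit cells | 10 | 0.40 | 0.29–0.40 |
| Four visits: 8 Shapiro–Wilk + 4 Levene | 12 | 0.46 | 0.36–0.48 |
| Five visits: 10 Shapiro–Wilk + 5 Levene | 15 | 0.54 | 0.39–0.55 |

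The simulated rates are for 15 or 21 per arm. The full range is therefore about 15–55%. It is about 40–55% only if every cell and every visit is checked and any single failure counts. At the 1% level the rates fall to 0.09–0.15.

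**2. Power of the planned test against the fallback**

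With n per arm, m visits and a constant effect d after baseline, the interaction test has noncentrality λ = (n/2) × d² × ((m − 1)/m) / (1 − ρ). Its degrees of freedom are m − 1 and (2n − 2)(m − 1).

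For n = 15 and m = 5: λ = 7.5 × 0.6561 × 0.8 / (1 − ρ) = 3.94 / (1 − ρ), with 4 and 112 degrees of freedom. This gives λ = 7.9, 13.1 and 19.7 at ρ = 0.5, 0.7 and 0.8. The noncentral F distribution gives power of 0.58, 0.82 and 0.95, in line with the simulated values below.

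| ρ | Planned interaction | Mann–Whitney, raw score, one visit | Mann–Whitney, change score |
|---|---|---|---|
| 0.5 | 0.57 | 0.53 | 0.55 |
| 0.7 | 0.83 | 0.53 | 0.75 |
| 0.8 | 0.96 | 0.53 | 0.90 |

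The raw-score test does not gain from correlation with baseline, so its power stays flat. The change-score test recovers most of the difference.

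**3. False positives**

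- A single Mann–Whitney test rejects in 4–5% of null trials.
- The two-stage rule with one Mann–Whitney test after a switch stays at about 5% (0.043–0.052).
- If every follow-up is tested uncorrected after a switch, the overall rate is about 6–9%. With 2,000 simulated trials, a rate near 9% carries a simulation error of about 1.96 × √(0.09 × 0.91 / 2000) = 0.013.
- Rates of 11–15% arise only if four uncorrected visit tests are always run, which the plan does not say.

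**4. Number of visits**

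Section 2.4 says "four distinct sample collections will be undertaken at the following intervals: Pre, Post-1 month, Post-3 months, and Post-6 months", against five time points in section 8.2.2. This discrepancy is a separate matter. With four visits the trigger rate is somewhat lower (table in step 1) and there are three follow-up tests rather than four.

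**The case against.** The strongest reply is that the article describes the switch loosely and that a fuller plan may tighten it. Mann–Whitney is given only as an example. Normality is judged partly from plots, so no mechanical rule need apply. A statistician blinded to allocation does the analysis. Each Mann–Whitney test is valid at its own level.

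Much of this stands, and it rules out three stronger readings that a reader might infer:

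- **That the switch would fire in about half of trials with normal data.** That needs 15 checks at 5% with any failure decisive. The article states neither the number, the level nor the rule.
- **That the fallback ignores baseline.** That is true of raw follow-up scores only. The text does not exclude change scores.
- **That the error rate is uncontrolled.** One Mann–Whitney test keeps its level. The excess comes only from several uncorrected visit tests, and its size is modest.

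The power loss also has to be measured against the planned ANOVA, not against an ANCOVA that the article does not plan. At ρ = 0.5 the loss is small.

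The reply does not remove the core. The article does state a data-driven replacement, names one that cannot test the planned interaction, and offers none that can. Blinding does not change which question the test answers.

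**Conclusion.** The concern holds in this limited form. The stated rule lets preliminary checks replace the primary group × time analysis of ODI with a test of a different question. The trigger, visit, score and correction are all left open.

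The chance of an unnecessary switch is about 15–55% with normal data and checks at 5%; the upper part of that range depends on checking every cell and visit. The cost in power runs from slight (0.57 to 0.53 at ρ = 0.5) to large (0.96 to 0.53 at ρ = 0.8) on raw scores, and is much smaller on change scores. False positives rise to about 6–9% only if all follow-ups are tested uncorrected after a switch.

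These sizes rest on 15 per arm, 0.81 read as a standardised mean difference present at every follow-up, and equal correlation between visits. The mismatch between the test and the question rests on none of them. The plan should be changed, but the point does not invalidate the trial.

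**What to change.** Delete the sentence that switches tests. State one primary ODI contrast, preferably adjusted for baseline ODI, and keep it whatever the Shapiro–Wilk or Levene results show. Adjusting for baseline is a preference; the essential change is that one contrast is fixed in advance.

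Check the residuals of that model, not raw scores by cell. If they are clearly non-normal, report a permutation p-value or a bootstrap interval for the same contrast as a sensitivity analysis, so that the question does not change.

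The cost is about two sentences of analysis wording and a slightly more technical sensitivity analysis. No patient procedure or visit changes. Data collection is planned to run to January 2027 (section 2.1), so the wording can be settled before unblinding.
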